### **5.3 Non-inclusion criteria**

The parents or legal representatives of children included in the study may withdraw their consent at any time without having to justify their decision, and without this affecting the follow-up of their child.

Children whose parents or legal representatives have withdrawn their consent will be excluded from the research. The data concerning these children, collected before the withdrawal of consent, will be used in the analysis.

## **6. STUDY PROCEDURE**

The procedure evaluated in the frame of the present study is the PSG conducted every 6 months from the age of 6 months in DS children in the *Screened Group*.

### **6.1 Polysomnography**

In PSG, breathing and sleep stages are recorded, and sleep quality is investigated via recordings of brain activity during sleep. It is used to diagnose OSA. All PSGs will be performed at the child's home, and the installation will be done by a sleep technician. This PSG will be carried out under conditions similar to those for PSG in hospitals, to ensure greater comfort for parents and their children.

The exam must be scheduled within the required time frame. If the PSG is unsuccessful, a 2nd PSG will be attempted in the child's home. If this 2nd attempt is unsuccessful, the child will have to spend a night at Necker-Enfants Malades Hospital in [name] unit to undergo PSG.

The following sensors will be installed:

- Elastic straps around the chest and stomach: these straps are used to record breathing by studying the movements of the rib cage and stomach;
- A microphone will be held in place at the base of the neck with surgical tape to record snoring and the flow of air through the throat;
- Another sensor fastened to the pyjamas will provide information on the child's position during sleep;
- A final sensor on the arm will provide information about the child's movements during sleep.

The following signals will also be recorded:

- Electroencephalography (EEG)
- Electromyography (EMG)
- Electrocardiography (ECG)
- Electrooculography (EOG)

Oxygen and carbon dioxide concentrations in the blood will be recorded via a sensor placed on the tip of the finger to measure oxygen concentration and a sensor on the ear or sole of the foot to measure carbon dioxide concentration. Measuring these two parameters will provide information on the impact of nocturnal breathing on gas exchanges.

[figure not shown]

This examination will be read and interpreted by the team at the Necker-Enfants Malades Hospital sleep centre. Depending on the results, treatment may be proposed by this team using the local practice, including ENT treatment (adenoidectomy and/or tonsillectomy) or CPAP treatment in the event of severe sleep breathing abnormalities and if ENT surgery is unsuccessful or not possible.

If OSA is detected at 30 months, ENT treatment and/or CPAP should be done no later than one month after screening, to allow a repeat check at 36 months and neuropsychological testing at 36 months  $\pm$  1 month after treatment and correction of OSA, for a duration of 5 months.

All these treatments will be carried out at the Necker-Enfants Malades Hospital. A follow-up PSG will be performed to check that the sleep disorders have been corrected. This control PSG will be either a systematic PSG scheduled as part of the study, or an additional PSG for medical reasons. Other visits and/or hospitalisations may be necessary for medical reasons. In all cases, the schedule of one PSG every 6 months must be complied with.

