### **3.3 Clinical experience**

Our sleep and non-invasive ventilation (NIV) unit cares for many newborns and infants with DS. If the sleep study reveals OSA, we adopt a "perfectionist" therapeutic attitude, which aims to completely normalise the sleep disorders observed. Depending on the case, this treatment involves ENT surgery and/or treatment with continuous positive airway pressure (CPAP) in the most severe cases. CPAP involves the delivery of continuous positive airway pressure using a CPAP machine and a mask that is held to the child's face by a small harness or cap. In the case of infants, a nasal mask is used. This CPAP treatment is only used during sleep (at night and during naps) because it is during sleep that airway obstruction is at its greatest. This CPAP treatment can be carried out at home, regardless of the child's age, after the child has adapted and the parents or care giver have received therapeutic training. This CPAP treatment is continued until sleep is completely normalised.

In our clinical experience, we found that infants who were effectively treated with CPAP for OSA from an early age had better neurocognitive and behavioural development than children of the same age who were not screened for OSA. We therefore wish to verify our hypothesis, which is that OSA is very common, under-diagnosed and therefore under-treated in DS infants, and that systematic screening and optimal correction of OSA during the first 3 years of life is associated with better neurocognitive and behavioural development at 3 years of age.

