## **4.4 Secondary endpoints**

- To demonstrate that screening for OSA by PSG and its treatment if necessary is associated with improved behaviour; the mean total scores and sub-scores of the Vineland Adaptive Behaviour Scales, Second Edition (VABS-II), Behaviour Rating Inventory of Executive Function – Preschool (BRIEF-P) and Child Behaviour Checklist - Preschool (CBCL-P) at the age of 3 years will be compared between the groups.
- To show that OSA is less frequent and less severe in the screened children; the number of children with OSA at the age of 3 years and the mean apnoea-hypopnoea index (AHI) at the age of 3 will be compared between the 2 groups;
- To show the value of peripheral saturation,  $\pm$  nocturnal transcutaneous carbon dioxide,  $\pm$  actigraphy,  $\pm$  suprasternal pressure sensor in predicting the presence of OSA with PSG.

- Parents' subjective sleep quality assessed using the Pittsburgh Sleep Quality Index (PSQI) and the Epworth Sleepiness Scale, and the child's subjective sleep quality assessed using the Children Sleep Habits Sleep Questionnaire;
- Assessment of language at 5 years, by analysis of the Quotient of Development for the Language subscale (QDL) of the Griffiths III, by analysis of the raw scores of the Naming and Word Comprehension tests of the Wechsler Preschool and Primary Scale of Intelligence - Fourth Edition (WPPSI-IV), a verbal fluency task (number of words produced in one minute) and by the CBCL-P language proxy questionnaire (number of words produced in French and a foreign language).
- Assessment of cognitive functions, by analysing the Composite Global Executive (CGE) Score and scores on the Inhibitory Control, Flexibility and Emerging Metacognition Indices, as well as the scores of the different sub-domains within each index obtained from the BRIEF-P scale;
- Assessment of behaviour by analysing the mean total scores and sub-scores obtained on the CBCL-P proxy questionnaire and the VABS-II.
- Finally, the results obtained from the Griffiths III, the BRIEF-P and CBCL-P proxy questionnaires and the VABS-II at 5 years will be compared with the results obtained at 3 years.

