### **5.2 Non-inclusion criteria**

- Child with a gestational age < 36 completed weeks of amenorrhoea
- Child presenting or having presented signs of acute central nervous system distress: Stroke, post-operative hypoxia, meningitis
- Child with DS already treated with CPAP for OSA
- Child participating in other interventional research involving humans or for whom participation in other interventional research involving humans is planned during the study duration
- Child whose parents do not understand the constraints related to the study
- Child whose parents plan to move outside the Paris region before the end of the study.

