### **7.2 Patients' recruitment**

The parents or legal representatives of children with DS will be contacted by telephone by the Institute's investigators to ask them to take part in the study. The ICF will be sent to them by post or email, allowing them a reasonable period of reflection between the telephone contact and the inclusion visit.

This same ICF will be presented orally by the investigator during the inclusion consultation at the IJL. Participation in the study will be offered to all infants under 6 months and all children aged 36  $\pm$  1 months, and the two groups will be recruited in parallel. Children who meet the eligibility criteria and whose parents or legal representatives sign the ICF after a sufficient period of reflection will be included. A copy of the ICF, dated and signed, will be given to those holding parental authority. The investigator will keep the original.

Children aged less than 6 months will form the *Screened Group*, and children aged 36  $\pm$  1 months the *Standard Care Group*.

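### The 36-month PSG does not measure OSA on the same basis in the two groups: its CPAP condition is not fixed, and CPAP bars controls at 36 months but Screened children only at 0 to 6 months

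*Protocol*

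**What the plan says.** **Role of the study PSG.** Section 6.1 provides for a PSG after treatment: "A follow-up PSG will be performed to check that the sleep disorders have been corrected". It continues: "This control PSG will be either a systematic PSG scheduled as part of the study", or else an extra PSG done for medical reasons. For OSA found at 30 months, the same section asks for ENT treatment and/or CPAP within a month, "to allow a repeat check at 36 months and neuropsychological testing at 36 months". By then the child is expected to be in a treated state, since the check and the testing come "after treatment and correction of OSA, for a duration of 5 months".

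**Duration of CPAP.** Section 6.1 leaves treatment to the local practice of the sleep unit. Section 3.3 describes that practice: "This CPAP treatment is continued until sleep is completely normalised". No end before 36 months is set.

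**Endpoint.** Section 4.4 compares "the number of children with OSA at the age of 3 years and the mean apnoea-hypopnoea index (AHI") at that age between the groups.

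**Eligibility.** Section 5.2 lists among its non-inclusion criteria: "Child with DS already treated with CPAP for OSA". Under sections 5.1 and 7.2, inclusion takes place at 0 to 6 months in the Screened Group and at 36 ± 1 months in the Standard Care Group.

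**Not fixed.** Sections 6.1, 7.3.10 and 11.5 do not say whether the 36-month PSG of a child on CPAP is made with the device on or off. Section 4.4 does not say how such a child counts.

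**The concern.** A Screened child who started CPAP after entry stays in the study and has the 36-month PSG. If that PSG is made under CPAP, a normal reading shows that the device works, not that the disease has gone, yet the child may be counted as free of OSA with a low AHI. A counterpart in the general clinic who is on CPAP at 36 months cannot enter the Standard Care Group at all. One group therefore keeps its CPAP-treated children, measured under an unstated condition, and the other has them removed.

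At stake is the secondary objective that OSA is less frequent and less severe at 3 years after screening. A difference could arise, or be hidden, through how and in whom OSA is measured.

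**Working it through.** **The plan's own figure.** With a difference of 8, SD 11.55, two-sided 5% and 80% power (section 9.1), n = 2 × (1.960 + 0.842)² × 11.55² / 8² = 32.7. That is 33 per group by the normal approximation and 34 by the t-test (33.7). Then 34 / 0.85 = 40. The stated 34 and 40 reproduce, and this point does not alter them.

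**Inputs for the illustration.**
- True OSA frequency without CPAP, p: 40–50% and equal in both groups. Section 3.1 gives about 30–50%; equality is an assumption.
- Children analysed: 34 Screened (40 less 15% attrition) and 40 controls, who are assessed at inclusion. This split is an assumption.
- Share of Screened recorded as normal under CPAP, c: 10–20%, or about 3 to 7 of 34. The protocol gives no figure.
- Share of would-be controls barred because they are on CPAP, e: 0, c/2 or c. This is an assumption.

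**If the PSG is recorded on CPAP.** The observed Screened frequency is p − c. The control frequency is (p − e)/(1 − e), because barred children leave both numerator and denominator. The table gives the probability of a two-sided 5% uncorrected chi-squared result favouring Screened, by exact enumeration of both binomial counts. The nominal rate is 2.5%.

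| c | e = 0 | e = c/2 | e = c |
|---|---|---|---|
| 10% | 13–14% | 9% | 5–6% |
| 15% | 25–28% | about 15% | 6–8% |
| 20% | 41–47% | 25% | 7–10% |

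Example, p = 40% and c = 10%: with e = 0, 30.0% against 40.0%, a spurious gap of 10 points. With e = 10%, the control frequency is (0.40 − 0.10)/0.90 = 33.3%, a gap of 3.3 points.

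At c = 5% the three columns are about 6%, 5% and 4%.

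**If the PSG is recorded off CPAP.** Screened shows p and controls still show (p − e)/(1 − e). The gap against Screened is e(1 − p)/(1 − e). At e = 10% it is 6.7 points for p = 40% (40.0% against 33.3%) and 5.6 points for p = 50%. At e = 20% it is 15.0 and 12.5 points.

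**Counting every child on CPAP as having OSA** gives the same Screened frequency, p, against the same depleted controls. It therefore carries the same 6 to 15 points against Screened when e is 10–20%. Adding the barred children back removes this: with 40 controls included and e = 10%, about 40 × 0.10/0.90 = 4.4 were barred, and (13.3 + 4.4)/(40 + 4.4) = 40%.

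No size is given for mean AHI, because the protocol states no AHI distribution.

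**The case against.** **Recording on CPAP is inferred.** A reader might conclude that the 36-month PSG is made under CPAP and that the bias must favour screening. The protocol does not say so. The treatments being checked include adenoidectomy and tonsillectomy, after which nothing is masked. The sensor lists mention no mask or device. Section 3.3 can be read the other way, since a normal recording under CPAP would not show that CPAP can stop. This stands: only the missing condition is established, and the direction depends on it.

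**The large rates need unbarred controls.** The 13–47% range ignores the exclusion that is half of the asymmetry. It also implies that 20% (10/50) to 50% (20/40) of OSA cases are on CPAP, whereas section 6.1 keeps CPAP for severe abnormalities where ENT surgery fails or is not possible. This stands, so the range is an upper bound. Against it, section 3.2 presumes under-diagnosis, so CPAP may be rarer among would-be controls and the net effect need not vanish.

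**A treatment-policy reading is possible.** The objectives concern screening together with treatment, so controlled OSA could count as absent. That is defensible, but it is not stated, and removing CPAP-treated children from one group would still break it.

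**Classification belongs in the SAP.** This is partly right: the counting rule could sit there, and treatments are already recorded. But the condition of an endpoint recording may be unrecoverable if it is not captured at the time, and the eligibility asymmetry is in the protocol itself.

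**Conclusion.** The point holds as a defect in two secondary endpoints. As written, OSA frequency and mean AHI at 3 years are not measured on the same basis in the two groups, because the CPAP condition of the 36-month PSG is open and the CPAP criterion acts at different ages.

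The direction is not fixed. Recording on CPAP favours Screened; recording off CPAP, with CPAP-treated controls barred, works against it. Under the assumptions above, the chance of a false significant result for screening is about 13–47% at most, 9–25% with half-equal barring and 5–10% with equal barring, against 2.5%. The CPAP and barred shares are assumptions, so these figures show what is possible and do not estimate what will occur.

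Two stronger readings are not supported. The documents do not show that screening's result is inflated. Nor does this mechanism reach the primary Griffiths III endpoint, since the PSG recording condition does not enter that score.

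**What to change.** - **e-CRF.** Record CPAP status at 36 months and whether each 36-month PSG was made with or without CPAP.
- **OSA frequency (sections 4.4 and 9.3.2).** Pre-specify two reports: as measured, and with children on CPAP at 36 months counted as having OSA. The second cannot stand alone as the main analysis, because it leans against Screened while CPAP-treated controls stay out.
- **AHI.** Summarise by recording condition. Use an earlier off-CPAP value only as a sensitivity analysis, since it may be years old for an endpoint defined at 3 years. Show CPAP use per group beside the result.
- **Controls not included.** Log how many otherwise eligible controls are not included because of CPAP, and add them in a sensitivity analysis of OSA frequency.
- **Conclusion.** Limit any claim of less frequent and less severe OSA to what holds in both analyses.
- **Reconcile** section 5.2 with the Synopsis (Population), section 7.1 and section 7.3, which expect some controls to have been treated for OSA before age 3.

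The cost is one or two e-CRF fields, a screening-log count and some wording. The secondary result may look less favourable to screening. No change to care is proposed.

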## **6.2 Concomitant treatments**

There are no specifications regarding authorised or prohibited treatments. Children taking part in the study will be able to receive any treatment indicated for their care. Treatments will be recorded in the case report form.

## **7. CONDUCT OF THE STUDY**

### **7.1 Study methodology**

This is an interventional, comparative, multicentre, open-label, minimal-risk study without drug (Etude Hors Produit de Santé (HPS)).

The Institut Jérôme Lejeune (IJL) is the coordinating centre.

The IJL and the Necker-Enfants Malades Hospital are the investigating centres.

The planned duration of the inclusion period is 24 months; it may be modified if necessary, at the sponsor's discretion.

The children in the *Screened Group* will be monitored until they are 36 months old. Each PSG will be carried out within 1 month. An additional 3 months may be necessary if the PSG at home is unsuccessful (2 months between the 1st PSG and the 2nd PSG at home and 1 additional month between the 2nd PSG at home and the one carried out at the Necker - Enfants Malades Hospital). Children in the *Standard Care Group* will not be followed prospectively, and data concerning their medical follow-up, including PSG and treatment of OSA before the age of 3 years, will be collected in their medical records. Their PSG at the age of 3 years will be carried out within 1 month. An additional delay of 3 months may be necessary if the PSG at home is unsuccessful (2 months between the 1st PSG and the 2nd PSG at home and 1 additional month between the 2nd PSG at home and the one carried out at the Necker - Enfants Malades Hospital).

The expected duration of the research is 5 years + 4 months maximum.

### **7.2 Patients' recruitment**

The parents or legal representatives of children with DS will be contacted by telephone by the Institute's investigators to ask them to take part in the study. The ICF will be sent to them by post or email, allowing them a reasonable period of reflection between the telephone contact and the inclusion visit.

This same ICF will be presented orally by the investigator during the inclusion consultation at the IJL. Participation in the study will be offered to all infants under 6 months and all children aged 36  $\pm$  1 months, and the two groups will be recruited in parallel. Children who meet the eligibility criteria and whose parents or legal representatives sign the ICF after a sufficient period of reflection will be included. A copy of the ICF, dated and signed, will be given to those holding parental authority. The investigator will keep the original.

Children aged less than 6 months will form the *Screened Group*, and children aged 36  $\pm$  1 months the *Standard Care Group*.

### **7.3 Visits and data collected**

Children in the *Screened Group*:

- They will be seen at a total of 4 visits, including a medical, neurocognitive and behavioural assessment at 3 years.
- They will benefit from 6 PSG performed at home by a sleep technician (or at the sleep unit at Necker-Enfants Malades Hospital in the event of 2 unsuccessful PSG at home).

During at-home PSG, the sleep technician will give parents:

- a questionnaire about the quality of their child's sleep
- 2 questionnaires about the quality of their sleep
- a monitoring sheet for the progress of the PSG

These questionnaires are to be completed by the parents and returned to the technician the following day.

The procedure for performing PSGs is described in the appendix of the protocol. This examination will be read and interpreted by the team at the Necker-Enfants Malades Hospital sleep centre. Depending on the results, treatment may be proposed by this team using the local practice, including ENT treatment (adenoidectomy and/or tonsillectomy) or CPAP treatment in the event of severe sleep breathing abnormalities and if ENT surgery is unsuccessful or not possible. All these treatments will be carried out at the Necker-Enfants Malades Hospital. A follow-up PSG will be performed to check that the sleep disorders have been corrected. This control PSG will be either a systematic PSG scheduled as part of the study, or an additional PSG for medical reasons. Other visits and/or hospitalisations may be necessary for medical reasons. In all cases, the schedule of one PSG every 6 months must be complied with. Treatments will be recorded throughout the follow-up.

- A clinical research nurse (CRN) from the IJL will make telephone calls every 2 months to the parents of the children taking part in this research to collect all the information on medical and surgical treatments and associated rehabilitation (physiotherapy, psychomotor therapy, speech therapy, palatal plate, osteopathy, etc.) received by the children, as well as any adverse events (AEs).

#### Children in the *Standard Care Group*:

- They will be seen at a consultation during which they will undergo a neurocognitive and behavioural assessment at 3 years of age.
- They will receive PSG at home (or at the sleep unit at Necker-Enfants Malades Hospital if PSG at home is unsuccessful twice).
- These children will not be monitored prospectively and their medical follow-up before the age of 3 will be collected from their medical records. This includes potential screening and treatment for OSA.

#### 7.3.1 Visit V0: inclusion

Before any examination, the patient's legal representatives will sign the ICF and the patient's eligibility will be confirmed. Parents (legal representatives) will be asked to bring their child's karyotype results to the visit. The following data will be collected:

- Patient's characteristics at birth

- Timing of DS diagnosis: pre- or post-natal and karyotype result
- Gestational age, birth weight, height and head circumference
- Medical history and associated pathologies
- Malformations
- Associated sensory deficits: deafness, blindness
- Clinical examination: weight, height, head circumference
- Residence and childcare
- Digestive symptoms
- Rehabilitation
- Blood test results if available (TSH, haemogram)

### 7.3.2 PSG at 6 ± 1 months (Screened Group children)

- PSG
- Children Sleep Habits Sleep Questionnaire
- Parents' subjective sleep quality (PSQI, Epworth scale)
- PSG progress monitoring sheet

### 7.3.3 Visit V1 at 12 ± 1 months (Screened Group children)

- Clinical examination
- Digestive symptoms
- ENT follow-up
- Blood test results if available (TSH, haemogram)
- Rehabilitation
- Investigator's judgment of sleep apnoea
- Apnoea observed by parents
- Medical and surgical treatments
- AEs

